### Other measures/covariates

To control for potential predictor or confounding effects, the following measures will be assessed: age, sex, profession (physician or nurse), type of professional (MIR, EIR, or tutor), year of residency for residents, time as a tutor, time working in AP for tutors, and teaching unit (TU).

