**Methods:**

The MINDUDD study is a multicentre cluster randomised controlled trial with three parallel arms. Six Teaching Units will be randomised to one of the three study groups: 1) Experimental Group-8 (EG8); 2) Experimental Group-4 (EG4) Control group (CG). At least 132 subjects will participate (66 tutors/66 residents), 44 in the EG8, 44 in the EG4, and 44 in the CG. Interventions will be based on the Mindfulness-Based Stress Reduction (MBSR) program, including some self-compassion practices of the Mindful Self-Compassion (MSC) programme. The EG8 intervention will be implemented during 8 weekly face-to-face sessions of 2.5 h each, while the EG4 intervention will consist of 4 sessions of 2.5 h each. The participants will have to practice at home for 30 min/day in the EG8 and 15 min/day in the EG4. The Five Facet Mindfulness Questionnaire (FFMQ), Self-Compassion Scale (SCS), Perceived Stress Questionnaire (PSQ), Maslach Burnout Inventory (MBI), Jefferson Scale of Physician Empathy (JSPE), and Goldberg Anxiety-Depression Scale (GADS) will be administered. Measurements will be taken at baseline, at the end of the programs, and at three months after completion. The effect of the interventions will be evaluated by bivariate and multivariate analyses (Multiple Linear Regression).

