### Assignment of interventions and randomisation

Cluster randomisation will be used, and each TU will be a cluster. Subject selection will be performed in each cluster and stratified by type of professional (66 tutors vs. 66 residents) between the CG (2 TU) and the two intervention groups (4 TU).

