### Statistical methods

The descriptive statistics of baseline characteristics of study participants and of questionnaire results—both before and after the intervention—will include means, standard deviations and ranges, medians and interquartile ranges, or frequencies and percentages, according to the variables. The fit of quantitative variables to the normal distribution will be checked by the Kolmogorov-Smirnov test. Prior to testing the effectiveness of the intervention, appropriate statistical tests will be used to examine possible baseline differences between groups (age, sex, time worked, profession, year of residency, previous mindfulness training). A per-protocol analysis will be performed in which all subjects who have completed at least 6 of the 8 sessions in EG8, or 3 of the 4 sessions in EG4, will be considered. All signalment analyses will be intention-to-treat in order to control for non-random dropout effects. Patterns of missing values ​​will be inspected and, if applicable, replaced using appropriate statistical methods.

To compare pre- and post-intervention results, a bivariate analysis will be performed, using Student’s t-test or the Wilcoxon test to compare related samples. Pre-post differences in the results of the questionnaires between the groups will be compared using ANOVA for repeated measures. Finally, a multivariate analysis will verify the effect of the interventions, adjusting for presumably predictive and/or confounding variables. To accomplish this, a multilevel linear regression will be used. The level of statistical significance will be set at *p* < 0.05 for all statistics. The analyses will be performed with SPSS version 17.0 and MLwiN version 3.00 software.

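### The between-group analysis rests on pre-post differences, the covariate list does not name the baseline score, and it lists the randomised teaching unit among the covariates

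*Protocol article*

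**What the plan says.** All references are to the protocol article.

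- **Covariates.** Other measures/covariates opens with "To control for potential predictor or confounding effects, the following measures will be assessed". It names age, sex, profession and type of professional, and ends with "year of residency for residents, time as a tutor, time working in AP for tutors, and teaching unit (TU". No baseline questionnaire score is named.
- **Between-group comparison.** Statistical methods first describes paired tests within groups ("To compare pre- and post-intervention results, a bivariate analysis will be performed"). It then compares the groups on their pre-post differences by repeated-measures ANOVA.
- **Adjusted model.** The last step is a multivariate analysis "adjusting for presumably predictive and/or confounding variables". The section continues: "To accomplish this, a multilevel linear regression will be used". MLwiN is one of the two software packages named. The section does not say which unit forms the upper level, or whether the baseline score enters. The Abstract calls the same analysis multiple linear regression.
- **Design.** "Six Teaching Units will be randomised to one of the three study groups" (Abstract). "Cluster randomisation will be used, and each TU will be a cluster", with TUs divided "between the CG (2 TU) and the two intervention groups (4 TU" (Assignment of interventions and randomisation). Sample size plans 22 participants per TU and 44 per arm.
- **Baseline data.** Under Data collection and data management, all groups are measured before the interventions start.

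**The concern.** Two features of the stated analysis work against it.

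First, the baseline enters the between-group comparison by subtraction, and nothing in the article says that it enters the regression. A change score takes off the whole baseline difference, although only part of it is expected to persist to follow-up. This costs precision whenever the pre-post correlation is below 1. It also over-corrects whatever imbalance arises by chance, and with two TUs per arm such imbalance is likely.

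Second, TU stands in the covariate list beside person-level variables such as age and sex, although every TU belongs to exactly one arm. What happens to the treatment effect then depends on whether TU enters as a random level or as a fixed term. The Methods and the Abstract name different models, and these point to different answers.

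**Working it through.** **The plan's own figure.** No stated figure is disputed here. The size per group reproduces from a difference of 15, SD 20, two-sided alpha 0.05 and power 0.80: 28 per group, and 28/0.75 = 37.3, rounded up to 38. It uses the full SD of 20, with no reduction for baseline.

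**1. Baseline as covariate or by subtraction.** With equal variances s² before and after and pre-post correlation r, the individual-level variance is s² for the follow-up score alone, 2(1−r)s² for the change score and (1−r²)s² after baseline adjustment. With two time points, the group-by-time test of repeated-measures ANOVA is the test on change scores. The ratio of adjusted to change-score variance is (1−r²)/[2(1−r)] = (1+r)/2. The documents give no r, so the range is assumed.

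| r | Follow-up only | Change | Baseline-adjusted | Adjusted / change | SE of change vs adjusted | SE of follow-up only vs adjusted |
|---|---|---|---|---|---|---|
| 0.3 | 1.00 | 1.40 | 0.91 | 0.65 | +24% | +5% |
| 0.5 | 1.00 | 1.00 | 0.75 | 0.75 | +15% | +15% |
| 0.7 | 1.00 | 0.60 | 0.51 | 0.85 | +8% | +40% |

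In participants, 1/0.65, 1/0.75 and 1/0.85 correspond to 54%, 33% and 18% more. This holds for the individual-level component only.

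**2. Allowing for the between-TU component.** At ICC 0.05 (the upper figure in Sample size) and 22 per TU, the design effect is 1 + 21 × 0.05 = 2.05. Of this, 22 × 0.05 = 1.10 is between TUs and 0.95 is individual. Suppose change scores also have ICC 0.05 and adjustment leaves the between-TU part untouched (both assumptions). The overall variance ratio is then (1.10 + 0.95 × 0.65)/2.05 = 0.84, and likewise 0.88 and 0.93 for r = 0.5 and 0.7.

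**3. Chance imbalance.** With the same inputs, the standard error of a baseline FFMQ difference between two arms is 20 × √(2 × 2.05/44) = 6.1 points. For an imbalance of d, the change score subtracts d and the adjusted analysis subtracts r·d, so the over-correction is (1−r)d. With d = 6.1 this is 4.3, 3.1 and 1.8 points for r = 0.3, 0.5 and 0.7, against a target difference of 15. This assumes that the individual-level slope also applies to TU means.

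**4. TU and arm.** Six TUs with 22 each and 44 per arm give two TUs per arm. Each arm indicator is then the sum of two TU indicators.

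- *TU fixed:* intercept + 2 arm + 5 TU indicators = 8 columns. The rank is 6, the same as for intercept and TU alone. Neither arm contrast is estimable.
- *TU random, arm fixed:* estimable. Over 300 simulated data sets (ICC 0.05, SD 20, true effect 15) the mean estimate was 15.1.

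**The case against.** The best defence is that the list records what is measured besides the outcomes. It is not presented as the full set of model terms, and a condensed article may leave exact terms to a fuller document. A baseline score is plainly predictive, so the open wording of Statistical methods does not exclude it, and baseline is already used through the pre-post differences. This stands to the extent that an unnamed baseline covariate is not, by itself, an error, and that change scores are unbiased under randomisation. It does not dispose of the point. The article does fix the between-group comparison on pre-post differences, and the purpose stated for the list matches the adjustment described for the regression.

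A reader might infer that the planned model cannot estimate the treatment effect at all. The documents do not support that. TU is defined as the cluster, the Methods specify a multilevel regression, and MLwiN is multilevel software. The natural reading is TU as the random level, and there the effect is estimable. Non-estimability arises only if TU enters as a fixed term. The covariate list and the Abstract's wording leave that open, but no section prescribes it.

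A reader might also infer that residency year and tutor time together leave none of the 132 participants with complete data. The list itself ties residency year to residents and time in primary care to tutors, and no section puts them into one pooled complete-case model.

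The objection that the 54%, 33% and 18% figures overstate the overall gain is fair. Step 2 of the working gives smaller gains once between-TU variance is counted.

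**Conclusion.** The point holds as a recommended change, not as a fatal flaw. Against change scores, naming the baseline score as a covariate removes 35%, 25% or 15% of the individual-level variance for r = 0.3, 0.5 or 0.7. Under the assumptions of step 2, about 16%, 12% or 7% of the overall variance goes. The gain is modest when r is high: the individual-level SE penalty of change scores is at most 15% once r reaches 0.5. Protection against over-correcting a chance imbalance is the second benefit. All these sizes rest on an assumed correlation.

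On TU, the defect is one of specification. A variable nested in arm is listed as a covariate, its role as the random level is never stated, and the Abstract and Methods name different models. The arm effect is lost only under the fixed-term reading.

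**What to change.** - Make the main between-group analysis the multilevel model, with the follow-up score as response; arm, the baseline score of the same questionnaire and type of professional (the stratum used in selecting participants) as fixed effects; and TU only as the random level-2 unit.
- Take TU out of the list of covariates, and say in Statistical methods that it is the level-2 unit.
- Replace multiple linear regression in the Abstract with the multilevel model.
- Keep the repeated-measures ANOVA on pre-post differences, if wanted, as a supporting analysis.

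Every variable is already collected and the software is already named, so the cost is wording. The change should be made before outcome data are examined.

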### Sample size

To calculate the sample size, we have drawn on a previous study [25], using as an outcome variable the mean FFMQ score [31]; accepting an alpha risk of 0.05 and a beta risk of 0.2, in a bilateral contrast, 38 subjects are required in each group to detect a difference ≥ 15 points in the FFMQ scale between both experimental groups (EG4 and EG8) and the CG. It is assumed that the common standard deviation is 20. A loss or withdrawal rate of 25% has been estimated [43]. Because this is a cluster randomisation study, we have considered the design effect. The design effect multiplies the sample size by a factor ranging from 1.5 to 3 to achieve the same power, depending on the relationship between intra- and intergroup variance [44]. Estimates of the intra-cluster correlation coefficient (ICC) in randomised clinical trials in AP are generally < 0.05 [45]. This ICC, for a cluster size of 15, results in a design effect corresponding to a factor of 1.7. Assuming this value, the final study sample size would be at least 130 subjects. One hundred and thirty-two (132) professionals will be included, 44 in each comparison group, 22 for each teaching unit.

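### The stated 80% power makes no allowance for having only two teaching units per arm; on the plan's own inputs a valid test has about 26% to 40% power at the planned size

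*Protocol article*

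**What the plan says.** All of this is in the protocol article.

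- **Sample size, error rates and target.** The calculation proceeds "accepting an alpha risk of 0.05 and a beta risk of 0.2, in a bilateral contrast", "to detect a difference ≥ 15 points in the FFMQ scale between both experimental groups (EG4 and EG8) and the CG". On variability: "It is assumed that the common standard deviation is 20". On attrition: "A loss or withdrawal rate of 25% has been estimated". The result is 38 per group.
- **Sample size, clustering.** The section says "The design effect multiplies the sample size by a factor ranging from 1.5 to 3 to achieve the same power", cites ICCs that are generally below 0.05, and concludes: "This ICC, for a cluster size of 15, results in a design effect corresponding to a factor of 1.7". It arrives at a minimum of 130 and plans 132, which is 44 per group and 22 per TU.
- **Assignment of interventions and randomisation.** "Cluster randomisation will be used, and each TU will be a cluster". Two TUs form the control group and four are shared by the two programme groups.
- **Statistical methods.** For the adjusted comparison of groups, "To accomplish this, a multilevel linear regression will be used". The section names neither the levels of the model nor the reference distribution for the arm contrasts.

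**The concern.** A design effect corrects the variance of an arm mean for clustering. It preserves the planned power only when there are enough clusters for 1.96 to remain the right critical value. Here each arm mean rests on two TUs, and two things follow that the calculation leaves out.

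First, the between-TU variance is estimated from very few units: 6 − 3 = 3 df if pooled over all six TUs, or 2 df from the two arms compared. The 5% critical value is then 3.18 or 4.30. Second, the between-TU part of the standard error does not shrink as more people are recruited inside the same TUs.

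The contrast affected is programme versus control on the FFMQ, which is the one the sample size is built on. A reader told that beta is 0.2 could give a non-significant result far more weight as evidence against an effect than this design supports.

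**Working it through.** **Inputs, all from Sample size and Assignment:** difference 15; SD 20; two-sided alpha 0.05; power 0.80; loss 25%; ICC 0.05 (implied by the factor 1.7); k = 2 TUs per arm; 22 enrolled per TU, so 22 × 0.75 = 16.5 analysed after loss.

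**1. The plan's own figures.**
- Per group: 2 × (1.960 + 0.842)² × (20/15)² = 27.9, rounded up to 28.
- After loss: 28/0.75 = 37.3, rounded up to 38, as stated.
- Design effect: 1 + (15 − 1) × 0.05 = 1.7, as stated.
- 38 × 1.7 = 64.6, rounded up to 65; 2 × 65 = 130, as stated. That is a two-group total, a separate matter.

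The number of clusters appears in none of these steps. At the planned cluster size the design effect would be 1 + 21 × 0.05 = 2.05, or 1 + 15.5 × 0.05 = 1.775 at 16.5 analysed.

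**2. Power with two TUs per arm.** With m analysed per TU:

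SE = √(2 × SD² × [ICC + (1 − ICC)/m] / k), noncentrality = 15/SE, and power from the noncentral t with 3 or 2 df.

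For ICC 0.05 and m = 16.5: SE = √(400 × [0.05 + 0.95/16.5]) = 6.56, noncentrality 2.29. With unlimited m: SE = √(400 × 0.05) = 4.47, noncentrality 3.35.

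| ICC 0.05, SD 20 | 3 df | 2 df | Normal approximation |
|---|---|---|---|
| 16.5 per TU | 36% | 26% | 63% |
| 22 per TU | 40% | 29% | 69% |
| 32.5 per TU (65 per arm, 195 in all) | 45% | 33% | 76% |
| Unlimited | 62% | 45% | 92% |

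Simulation of the TU means (400,000 runs) agreed: 39.7% and 29.3% at 22 per TU, 61.9% and 45.1% in the limit.

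**3. Lower ICCs (SD 20).**

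| ICC | 16.5 per TU, 3 df | 16.5 per TU, 2 df | Unlimited, 3 df | Unlimited, 2 df |
|---|---|---|---|---|
| 0.03 | 41% | 30% | 81% | 62% |
| 0.02 | 45% | 33% | 93% | 76% |
| 0.01 | 49% | 36% | over 99% | 94% |
| 0 | 54% | 40% | – | – |

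With all 22 analysed, ICC 0 gives 66% (3 df) or 48% (2 df).

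**4. Baseline adjustment.** The article gives no pre-post correlation. Assume that a correlation r reduces both variance components by the factor 1 − r². At r = 0.8 and ICC 0.05, power is 72% (3 df) or 53% (2 df) at 16.5 per TU, and 77% with 3 df at 22. Combining r = 0.8 with ICC 0.01 at 16.5 per TU gives noncentrality 2.835/0.6 = 4.73, and so about 87% (3 df) or 68% (2 df).

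**The case against.** **A z test can reach 80%.** With 1.96 as the critical value, 80% is reached at about 44 analysed per TU at ICC 0.05. That is twice the planned enrolment per TU; at the planned size the normal approximation gives 63% to 69%. In simulation, using 1.96 on these few TU means gave a type I error of about 14% (3 df) or 19% (2 df), so that power is not at the stated alpha.

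**The ICC may be lower.** This stands in part. A reader might infer that this design cannot reach 80% power whatever the recruitment, or that a valid test would always miss a 15-point difference more often than it found it. The documents support neither. The article describes ICCs as generally below 0.05, so 0.05 is the upper end. With unlimited participants and 3 df, 80% becomes attainable at an ICC of about 0.031 or less (about 0.018 with 2 df). Power also passes 50% at the lowest ICCs, for example 54% at ICC 0 with 16.5 per TU. The 62% and 45% ceilings belong to ICC 0.05 and SD 20.

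**Baseline adjustment could help.** This also stands in part. The article does not say whether 20 is the SD of a score or of a change, and it plans baseline measurement and adjusted models. A strong correlation together with a low ICC could lift the planned size past 80% with 3 df. The sample-size calculation claims neither, and no correlation is given.

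**The degrees of freedom belong in the analysis plan.** The choice between 2 and 3 df can properly be left there, and the article does not fix the model's levels. The point does not depend on that choice. It concerns a power statement made in the article for a design that the article also fixes.

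**Nothing says that a null result would be read as no effect.** That is correct; it is a risk for readers, not a stated intention. The trial's main hypothesis also compares the two programmes with each other, a contrast this point does not address.

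**Conclusion.** The concern holds, with conditions. The arithmetic behind 38 and 1.7 is right for what it computes; the fault is treating that inflation as enough to preserve 80% power with two TUs per arm. On the plan's own inputs, power for the programme-versus-control contrast is 26% to 36% after the expected loss and 29% to 40% without loss. Without credit for baseline adjustment, the planned size misses 80% at every ICC from 0 to 0.05. A correlation of 0.8 alone does not close the gap at ICC 0.05.

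These figures assume a test that holds the two-sided 5% level with TU as the unit, equal TU sizes, and SD 20 on the analysis scale. Correcting the total to 195 would not resolve the matter: with all 65 per arm analysed, power at ICC 0.05 is 45% (3 df). The stated error rate should be corrected before results are interpreted.

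**What to change.** In Sample size, replace the statement that the design effect preserves 80% power with the power for two TUs per arm at the planned cluster size (22 enrolled, about 16.5 analysed). Show it as a range over ICC 0.01 to 0.05 and over 2 and 3 df. With SD 20 and 16.5 analysed per TU, that is 36% to 49% with 3 df and 26% to 36% with 2 df. State whether 20 is the SD of a score or of a change, and what baseline correlation, if any, is assumed.

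In Statistical methods, add that the programme-versus-control contrasts will be reported as estimates with confidence intervals on cluster-level degrees of freedom, and that a non-significant contrast will not be read as absence of effect.

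The cost is a rewritten paragraph and one added sentence. Recruitment and conduct do not change, and no further participants or TUs are requested. The downside is that the stated power becomes much less favourable.

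### The final sample size of 130 matches a two-group total but is spread over three arms, so 44 per arm gives about 63–65% power at the protocol's own planning values, not 80%

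*Protocol article*

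**What the plan says.** All the figures stand in the Sample size section of the protocol article.

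- Error rates: "accepting an alpha risk of 0.05 and a beta risk of 0.2, in a bilateral contrast".
- Base number: "38 subjects are required in each group", to detect a difference of at least "15 points in the FFMQ scale between both experimental groups (EG4 and EG8) and the CG", with a common SD of 20.
- Loss: 25%.
- Clustering: the ICC is described as generally below 0.05, and "This ICC, for a cluster size of 15, results in a design effect corresponding to a factor of 1.7".
- Result: "Assuming this value, the final study sample size would be at least 130 subjects".
- Allocation: "One hundred and thirty-two (132) professionals will be included, 44 in each comparison group, 22 for each teaching unit".

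The Abstract and the Study design section describe three parallel arms. The section on assignment and randomisation places two teaching units (TUs) in the control group and four across the two intervention groups.

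**The concern.** The paragraph states a requirement per group, says that it is multiplied by a design effect, and gives a total. With three equal arms, that total should be three times the inflated group size. Dividing 132 by three instead gives 44 per arm. This exceeds the pre-clustering figure of 38 by a factor of only 44/38 = 1.16, although the stated factor is 1.7.

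At stake is the beta of 0.2. If the design does not deliver it, a non-significant comparison with control could be read as evidence of no effect when the chance of missing a 15-point difference was well above 20%. The results paper would also carry forward a power claim that does not follow from its inputs.

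**Working it through.** **1. Reproduce the 38.** Inputs from the Sample size section: difference 15, SD 20, two-sided alpha 0.05, power 80%.

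n = 2 × (1.96 + 0.8416)² × 20² / 15² = 27.9, rounded up to 28 per group.

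With 25% loss: 28 / 0.75 = 37.3, rounded up to 38. This is the stated figure, so 38 already contains the loss.

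**2. Reproduce the design effect.** DE = 1 + (15 − 1) × 0.05 = 1.70, as stated.

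**3. Reproduce the 130.** 38 × 1.7 = 64.6, rounded up to 65 per group.

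| Route | Total | Matches 130? |
|---|---|---|
| 2 × 38 × 1.7 | 129.2 (130 at 65 per group) | yes |
| 3 × 38 × 1.7 | 193.8 (195 at 65 per arm) | no |
| 3 × 28 × 1.7 (no loss allowance) | 142.8 | no |
| 3 × 38 (no design effect) | 114 | no |

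A one-sided test would need 22 before loss, which does not lead to 38 (22 / 0.75 = 29.3). A Bonferroni correction for three comparisons would give 38 before loss, but 3 × 38 × 1.7 is still 193.8.

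**4. Power with 44 per arm.** With n analysed per arm:

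Power = Φ(15 / (20 × √(2 × DE / n)) − 1.96).

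After 25% loss, n = 44 × 0.75 = 33 per arm, or 16.5 per TU.

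- DE 1.7: effective n = 33 / 1.7 = 19.4 against the 28 needed. The standard error is 20 × √(3.4 / 33) = 6.42, and power = Φ(2.34 − 1.96) = 64.7%.
- DE at 16.5 analysed per TU: 1 + 15.5 × 0.05 = 1.775. Effective n = 18.6, the standard error is 6.56, and power = Φ(2.29 − 1.96) = 62.8%.

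As a check, 65 per arm with 25% loss and DE 1.7 gives an effective n of 28.7 and power of 81%, so the formula agrees with the protocol's target.

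**5. Difference detectable with 80% power.** 2.80 × 6.42 = 18.0 points (DE 1.7); 2.80 × 6.56 = 18.4 points (DE 1.775).

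**6. Sensitivity, 44 enrolled per arm.**

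| Loss | ICC or DE | Power for 15 points |
|---|---|---|
| 25% | DE 1.7 | 65% |
| 25% | ICC 0.05, DE 1.775 | 63% |
| 20% | DE 1.7 | 67% |
| none | DE 1.7 | 77% |
| none | ICC 0.05, 22 analysed per TU, DE 2.05 | 69% |
| 25% | ICC 0.02, DE 1.31 | 76% |
| 25% | ICC 0.01, DE 1.155 | 81% |

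**7. Few clusters.** The figures above use a normal quantile. If the 25%-loss, DE 1.775 case is referred to a t distribution on 3 df (six TUs less three arms), power is about 36%.

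**The case against.** Several objections have force.

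- **ICC and loss could be kinder.** The protocol gives 0.05 as an upper bound, and its Strengths and limitations section speaks of losses up to 20%. A reader might infer that 63–65% is the most the trial could have. It is not: the table shows 77% with no loss and 81% with ICC 0.01. But the protocol adopts 1.7 and 25%, and its 80% has to be judged against those values.
- **Baseline adjustment may help.** The Statistical methods section plans pre-post comparisons and an adjusted multilevel model. Suppose SD 20 is the SD of the post-score, and adjustment multiplies the variance by 1 − r² with the design effect unchanged. Power at DE 1.7 and 25% loss is then 69%, 77% or 83% for r = 0.3, 0.5 or 0.6. The protocol gives no r and does not use one in its calculation. So the stated calculation does not yield 80%, but it would go too far to say that the trial could not reach it.
- **The comparison might be pooled.** If both programmes together are compared with control (66 against 33 analysed), DE 1.7 gives Φ(15 / (20 × √(1.7 × (1/66 + 1/33))) − 1.96) = 77%. That is still below 80%, and a requirement of 38 in each group does not fit this reading.
- **Cluster size 15 against 22.** After 25% loss this is a small matter: 1.775 instead of 1.7, or two percentage points of power. A reader might combine DE 2.05 with 33 analysed per arm and arrive at 57%. That assumes 22 and 16.5 analysed per TU at once, so it should not be used.
- **38 before loss.** A reader might inflate 38 again for loss and reach 38 × 1.7 / 0.75 × 3 = 258. Step 1 shows that the loss is already in the 38.
- **The 36% depends on a model choice.** The protocol fixes no degrees of freedom, and 2 df would give 26–27%. Having two TUs per arm is a real weakness of the design, but it is separate from the arithmetic error.
- **The origin of 130 is inferred.** The match with two groups is close and no other route tried gives it, but the protocol does not say how 130 was obtained.

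**Conclusion.** The stated total does not follow from the stated inputs for a three-arm trial. They require 65 per arm, about 194–195 in total; the trial enrols 44 per arm. At the protocol's planning values (25% loss, ICC 0.05), power for a 15-point difference between one programme and control is about 65% (DE 1.7) or 63% (DE 1.775). The type II error is therefore roughly 0.35 to 0.37 instead of 0.2, and 80% power is reached only at about 18 points.

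This rests on an unadjusted comparison of two means with SD 20 under the normal approximation. The size of the shortfall depends on ICC, loss and adjustment, and in the most favourable case in the table (ICC 0.01) it disappears. A small-cluster reference would move it substantially the other way. The check concerns superiority over control only and says nothing about the non-inferiority comparison of the two programmes.

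**What to change.** Keep enrolment as planned and correct the paragraph:

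1. Show 28 per group before loss and 38 after.
2. Reconcile 130 with three arms. If it was computed for two groups, say so, and give the 65 per arm (194–195 in total) that the same inputs imply.
3. Use a design effect consistent with the planned cluster size: 1.775 at 16.5 analysed per TU, and 2.05 only if all 22 are analysed.
4. Replace the 80% claim with what 132 participants deliver at the planning values: about 63–65% power for 15 points, or 80% power for about 18 points. Give the range over ICC and loss.
5. Note that these are normal-approximation figures and that, with two TUs per arm, a cluster-level t reference gives substantially lower power (about 36% on 3 df).

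The figure of 195 should not be read as a simple cure within the same six TUs, because larger clusters raise the design effect. With 65 per arm and 25% loss, 24.4 are analysed per TU, DE = 1 + 23.4 × 0.05 = 2.17, effective n = 48.75 / 2.17 = 22.5, still below 28.

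The cost is one reworded paragraph and a less favourable stated power. No participants are added and the analysis does not change.
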